## Formulation of Test and Control Products

Both test and control treatment groups will receive 25mL of Ropivacaine 0.5%, a local anesthetic that is approved for peripheral nerve block use. Ropivacaine is a clear colored solution that requires no reconstitution. There is no placebo comparator in this study as it would be unethical given the analgesic benefits of interscalene block for shoulder surgery. As the drug is the same for each group, it is not necessary for it to be blinded.

## Supply of Study Drug at the Site

As the study drug is a commonly used medication for peripheral nerve block, it is readily available at the study site.

### Dosage/Dosage Regimen

25mL of ropivacaine 0.5% given for interscalene block once. No adjustments for age. This dose must not exceed a max dose of 3.5mg/kg of ropivacaine.

Dispensing

The anesthesia provider performing the block will prepare and dispense the drug.

### Administration Instructions

**For the placement of the interscalene block, the patient may receive any of the following medications:**

- Midazolam: 0-4mg IV
- Fentanyl: 0-100mcg IV
- Ropivacaine 0.5%: 25mL for interscalene block

**For the induction of general anesthesia:**

- Lidocaine: 0-100mg IV
- Propofol: as much as necessary for IV induction
- Fentanyl: 0-50mcg IV for LMA insertion

**For the maintenance of general anesthesia:**

- Sevoflurane or desflurane per anesthesia provider.
- Propofol gtt between 25-100mcg/kg/min per anesthesia provider.

**For IntraOperative Analgesia:**

- Fentanyl: as needed at anesthesia provider's discretion.
- No Ketorolac or Hydromorphone (IntraOp).

**For IntraOperative PONV prophylaxis:**

- Dexamethasone: 4mg IV after induction
- Ondansetron: 4mg IV prior to emergence

**For recovery room orders:**

- Fentanyl: 0-350mcg PRN pain
- Ketorolac 30mg x1 in PACU only
- No hydromorphone orders until evaluated by study personnel
- Ondansetron: 4mg IV (2nd dose)
- Prochlorperazine 10mg IV x1 dose
- Metoclopramide 10mg IV x1 dose
- Meperidine up to 50mg for shivering

## Supply of Study Drug at the Site

The study drug is a commonly used local anesthetic that is readily available at the study site.

### Storage

Study drug should be stored by the study site at controlled room temperature, 15 to 30ºC (59 to 86ºF). If the temperature of study drug storage in the clinic/pharmacy exceeds or falls below this range, this should be reported to the Principal Investigator or designee and captured as a deviation. Subjects will be instructed to store the medication in original packaging (foil pouch and protected from light) at room temperature according to the instructions outlined on the Drug Administration Instructions.

## Study Drug Accountability

An accurate and current accounting of the dispensing and return of study drug for each subject will be maintained on an ongoing basis by a member of the study site staff. The amount of study drug dispensed will be recorded in the Medication Administration Record.

# STUDY PROCEDURES AND GUIDELINES

A Schedule of Events representing the required testing procedures to be performed for the duration of the study is diagrammed in Appendix 1.

Prior to conducting any study-related activities, written informed consent and the Health Insurance Portability and Accountability Act (HIPAA) authorization must be signed and dated by the subject. If appropriate, assent must also be obtained prior to conducting any study-related activities.

## Clinical Assessments

### Concomitant Medications

All concomitant medication and concurrent therapies will be documented at screening and on study day 1 (day of surgery), postoperative day 1, and at early termination when applicable. Dose, route, unit frequency of administration, and indication for administration and dates of medication will be captured.

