## Secondary Efficacy Endpoints

- Time to onset of sensory block – evaluated by detection of decreased sharpness of contralateral side. This will be evaluated for supraclavicular, axillary, musculocutaneous, median and ulnar nerve distributions.
- Duration of nerve blockade (time from block completion to time patient reports the block started to wear off and no longer providing pain relief)
- Highest pain score in the post-anesthesia recovery unit (using numerical rating scale from 0-10 pain, 0 is no pain, 10 is worst imaginable pain)
- Highest pain score on postoperative day 1 (using numerical rating scale from 0-10 pain, 0 is no pain, 10 is worst imaginable pain), at rest and with movement
- Block performance time - time from block needle insertion to the time that all of the local anesthetic was injected
- Patient satisfaction score – scale from 0-10. Zero is unsatisfied. 5 is neutral and 10 is extremely satisfied.
- Perioperative opioid use – total opioids used preoperative, intraoperative, and postoperatively will be recorded
- Perioperative analgesic consumption – acetaminophen, ibuprofen, ketorolac usage perioperatively
- Number of needle passes - number of times the needle was re-advanced after being withdrawn during block placement
- Block failure - lack of sensory exam consistent with interscalene block in the recovery room or need for repeat interscalene block in recovery room
- Recovery room length of stay (time from entering recovery room to time that discharge criteria met)
- Highest pain score at one week postoperative week visit (0-10 with zero being no pain and 10 worst imaginable pain)

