## Exclusion Criteria

1. Pregnant during participation in the study.
2. Non-English speaking
3. Any contraindication for regional anesthesia, such as an allergy to local anesthetics or opioids, coagulopathy or severe thrombocytopenia, infection at puncture sites, pre-existing neuropathy in operative limb, need for postoperative nerve function monitoring
4. History of pulmonary disease or low baseline oxygen saturation
5. History of dementia
6. High preoperative opioid requirements

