# Concurrent Medications

All subjects should be maintained on the same medications throughout the entire study period, as medically feasible, with no introduction of new chronic therapies.

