# STUDY TREATMENTS

## Method of Assigning Subjects to Treatment Groups

Up to 208 eligible patients will be randomly assigned to intraplexus or extraplexus treatment groups in a 1:1 ratio using an Excel computer-generated randomization scheme developed by the study data management provider. The allocated group will be written on a paper in a sealed, opaque envelope that will be provided only to the anesthesia provider performing the block.

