## Analysis of Secondary Endpoints

Categorical data will be analyzed using Chi squared analysis or Fischer's exact test, depending on sample size. Comparison of means will be performed using the independent sample t-test or the Mann-Whitney U test, depending on distribution. A p-value of 0.05 or smaller will be considered statistically significant.

Safety and tolerability data will be summarized by treatment group. Adverse event rates will be coded by body system and MedDra classification term.  Adverse events will be tabulated by treatment group and will include the number of patients for whom the event occurred, the rate of occurrence, and the severity and relationship to study drug.

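### Perioperative opioid use is compared without adjustment for preoperative opioid use, although the medication record taken before randomization would allow it: a small, avoidable loss of precision on one secondary endpoint

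*Protocol*

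**What the plan says.** - **Hypothesis.** The protocol synopsis (Secondary Objectives) expects the intraplexus approach to reduce opioid consumption through a longer block.
- **Endpoint.** Secondary Efficacy Endpoints defines perioperative opioid use as "total opioids used preoperative, intraoperative, and postoperatively will be recorded".
- **Who can enroll.** Exclusion Criteria bars "High preoperative opioid requirements" and gives no threshold.
- **What is recorded.** The Concomitant Medications part of Clinical Assessments states: "All concomitant medication and concurrent therapies will be documented at screening and on study day 1 (day of surgery), postoperative day 1". It adds that "Dose, route, unit frequency of administration, and indication for administration and dates of medication will be captured". In the Visit 1 list, the medication record is item 5 and randomization is item 11.
- **Background medication.** Concurrent Medications: "All subjects should be maintained on the same medications throughout the entire study period, as medically feasible".
- **Allocation.** Patients are "randomly assigned to intraplexus or extraplexus treatment groups in a 1:1 ratio"; no stratification is described.
- **Analysis.** Section 14.4: "Comparison of means will be performed using the independent sample t-test or the Mann-Whitney U test, depending on distribution", and "A p-value of 0.05 or smaller will be considered statistically significant". No covariate is named. The baseline list in section 14.2 (gender, age, height, weight, BMI and some surgical characteristics) does not include preoperative opioid use.

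**The concern.** Patients who already take some opioid before surgery are likely to use more around it. Where such patients are enrolled, the difference between users and non-users adds to the spread within each arm. A two-sample t-test or Mann-Whitney test leaves that spread in the standard error, while a comparison adjusted for preoperative use takes it out. The covariate is measured before randomization, so adjusting for it is safe, and the protocol already collects it. At stake is the width of the confidence interval for one named secondary hypothesis. In addition, because section 14.2 omits the variable, the planned baseline summary would not show a chance imbalance in prior users.

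**Working it through.** **Plan's own figures.** The protocol gives no SD, effect size or power for opioid use, so there is nothing to reproduce for this endpoint. Its only sample-size figure is for the primary endpoint. With hazard ratio 0.65, two-sided alpha 0.05 and power 0.80, Freedman's formula gives (1.960 + 0.842)² × (1.65/0.35)² = 174.4, so 175 events; Schoenfeld's gives 170. Both are within 3% of the stated 172. The present point does not touch that figure.

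**Inputs.**
- From the protocol: 104 per arm, 1:1 allocation, alpha 0.05 (sidedness is not stated in section 14.4; two-sided assumed).
- Assumed, because the protocol does not give them: p, the share of prior opioid users enrolled, and d, the user-minus-nonuser difference in total opioid use, in SDs within user group. Lower case: p = 0.10, d = 0.5. Upper case: p = 0.20, d = 1.

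**Validity of the planned test.** The unadjusted t-test was simulated with no treatment effect, 104 per arm, d = 1 and 10,000 runs per setting. Rejection rates were 0.048, 0.052 and 0.049 with 5%, 10% and 20% users. Type I error is held.

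**Variance that adjustment removes.** Total variance is 1 + p(1−p)d², so the removable share is p(1−p)d² / (1 + p(1−p)d²).
- Lower: 0.10 × 0.90 × 0.25 = 0.0225; 0.0225/1.0225 = 2.2%.
- Upper: 0.20 × 0.80 × 1 = 0.16; 0.16/1.16 = 13.8%.

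The unadjusted analysis would need p(1−p)d² more patients for the same precision: about 2% in the lower case and 16% in the upper.

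**Detectable difference at 80% power, in total SDs.**
- Unadjusted: (1.960 + 0.842) × √(2/104) = 0.389.
- Adjusted, lower: 0.389 × √(1 − 0.022) = 0.384.
- Adjusted, upper: 0.389 × √(1 − 0.138) = 0.361.

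**Chance imbalance, upper case.**
- SD of the between-arm difference in the share of users: √(2 × 0.16/104) = 0.055.
- Exceeded in absolute value in about 1 trial in 20: 1.96 × 0.055 = 0.109, or 11 percentage points.
- Shift in the arm difference at d = 1: 0.109 within-group SD.
- Standard error of the unadjusted difference: √1.16 × √(2/104) = 1.077 × 0.139 = 0.149.
- Ratio: 0.109/0.149 = 0.73 standard errors.

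These formulas are for a linear model. They indicate the order of the gain for a rank test but do not give it exactly.

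**The case against.** The strongest objection is that nothing is wrong with the planned test. Randomization makes it valid, and its standard error already allows for chance imbalance in any baseline factor. The 0.73 standard errors are part of ordinary sampling variation that the p-value covers. This stands. A reader might infer that an imbalance in prior users biases the comparison or inflates false positives; the simulation shows no inflation.

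A reader might also infer that habitual opioid doses are counted in the endpoint. The protocol does not say so. Neither Concomitant Medications nor Concurrent Medications names opioids, and the latter is qualified by medical feasibility. In the endpoint definition, preoperative opioids could mean the fentanyl allowed for block placement. The point needs only that prior use predicts the total, not that it is contained in it.

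A larger gain is tempting too: 30% users at 1.5 SD would give 0.473/1.473 = 32% of the variance. Nothing in the protocol supports that once high users are excluded and entry is limited to ASA I-II ambulatory patients. Nor should the shift be divided by 0.139, which gives 0.78: that is the standard error after prior use has been removed, not that of the planned test.

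Finally, section 14 says the SAP will contain any modifications to the plan. That permits a change but does not make one. Section 14.4 names the tests, so this is a stated choice that can be improved rather than a gap left for the SAP.

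**Conclusion.** The point holds as a minor one. For a stated secondary hypothesis, section 14.4 names tests that cannot use a prognostic value the trial already records before randomization. The consequence is lost precision on one secondary endpoint that has no power calculation of its own. The primary log-rank analysis and the sample size of 208 are not affected. The size rests wholly on assumed p and d: about 2% of the variance at 10% users and 0.5 SD, and about 14% at 20% users and 1 SD. If very few users enroll, the gain is negligible. Pain scores might benefit in the same way, but nothing here quantifies that.

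**What to change.** In section 14.4, or in the SAP before unblinding, name one baseline-adjusted comparison for perioperative opioid use. Two suitable choices are:
- a van Elteren test stratified by preoperative opioid use (yes/no), which suits a skewed total with many zeros;
- a linear model on the log-transformed total with treatment and preoperative opioid use as terms, stating how zero totals are handled.

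Fix the choice in advance rather than after looking at the distribution. Take preoperative use from the medication record made before randomization, and add it to the baseline summary in section 14.2. Applying the same adjustment to the pain scores is optional.

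The cost is one sentence in the analysis section, one baseline row and the coding of a variable from data already collected. No new patients or assessments are needed.

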### Demographics

Demographic information (date of birth, gender, race) will be recorded at Screening.

### Medical History

Relevant medical history, including history of current disease, other pertinent respiratory history, and information regarding underlying diseases will be recorded at Screening.

### Physical Examination

A complete physical examination will be performed by either the investigator or a subinvestigator who is a physician at Visit #1. Qualified staff (MD, NP, RN, and PA) may complete the abbreviated physical exam at all other visits. New abnormal physical exam findings must be documented and will be followed by a physician or other qualified staff at the next scheduled visit.

### Vital Signs

Body temperature, blood pressure, pulse and respirations will be performed after resting for 5 minutes on Visit day 1.

### Oximetry

Oximetry will be measured on room air with the subject at rest at Visit 1.

### Other Clinical Procedures

**Interscalene nerve block:**

Patients at the Orthopaedic Institute undergoing shoulder arthoscopy typically receive a preoperative ultrasound-guided interscalene nerve block. Patients in the control group will have local anesthetic injected circumferentially around the interscalene brachial plexus. Patients in the experimental group will have a single injection of local anesthetic placed inbetween the C5- C6 nerve roots. Light sedation is usually administered via the patient's IV during performance of the block. These blocks are performed in the preoperative holding area, with the patients receiving continuous non-invasive blood pressure and pulse oximetry monitoring until being transported into the operating room.

An study investigator (not involved in block placement) will assess motor and sensory block until the onset of block or until the patient is taken to the operating room. From this point forward, patients in both groups are treated identically. All patients will subsequently undergo a general anesthestic.

Postoperatively, if the patient has poor pain control with intravenous opioids, they will be evaluated by an anesthesiologist. A nerve block may be repeated postoperatively if deemed necessary. This nerve block occurs in the post anesthesia recovery unit under continuous noninvasive blood pressure and pulse oximetry monitoring. Patients requiring postoperative nerve blocks will continue to participate in the study, and the number of patients requiring such blocks will be tabulated and analyzed as one of our outcome variables. All patients will be asked to rate their pain and will be provided a pain diary while in the recovery unit.

On postoperative day 1, an anesthesiologist will call the patient and review the questions on the pain diary and solicit responses from the patient. The patient will not be asked to return the pain diary -- it is meant to serve as a guide for the patient as to what questions they will be asked during these brief, approximately 5 minute, phone calls. If the patient's block has not yet resolved by the time of the follow-up phone call on postoperative day 1, then the patient will be called daily until resolution of their block, typically by postoperative day 2.

The patients will be seen by the orthopedic surgery team on 1 week postoperatively and will be assessed for any adverse events as well as their highest pain score.

### Adverse Events

Information regarding occurrence of adverse events will be captured throughout the study. Duration (start and stop dates), severity/grade, outcome, treatment and relation to study drug will be recorded on the case report form (CRF).

### Pregnancy Test

A urine pregnancy test will be obtained from female subjects who are of childbearing age prior to their participation in the study.

# EVALUATIONS BY VISIT

## Visit 1 (Day of surgery)

1. Review the study with the subject and obtain written informed consent and HIPAA authorization and assent, if appropriate.
2. Assign the subject a unique screening number.
3. Record demographics data.
4. Record medical history.
5. Record concomitant medications.
6. Perform a complete physical examination.
7. Perform and record vital signs.
8. Perform and record oximetry.
9. Perform and record results of blood pressure testing.
10. Collect urine for pregnancy test if applicable.
11. Randomize subject.
12. Perform interscalene block.
13. Assess subject for onset of motor and sensory blockade prior to entering operating room.
14. Assess subject for sensory blockade in recovery room.
15. Assess subject for any adverse events.
16. Record medications used intraoperatively and postoperatively.
17. Initiate subject diary.

## Visit 2 (postoperative day 1)

1. Record any Adverse Experiences and/or Review subject diary for adverse experiences and dosing compliance.
2. Concomitant medications review.
3. Record pain medications.
4. Record patient satisfaction, incidence of postoperative nausea and vomiting.
5. List all additional procedures.

## Visit 3 (postoperative week 1)

1. Record any Adverse Experiences and/or Review subject diary for adverse experiences.
2. Record changes to concomitant medications.
3. Perform abbreviated physical examination.
4. Perform and record vital signs.
5. Assess pain score.

## Early Withdrawal Visit

1. Record any Adverse Experiences and/or Review subject diary for adverse experiences and exclusionary medication use.
2. Record changes to concomitant medications.
3. Perform and record vital signs and physical exam.

# ADVERSE Experience REPORTING AND DOCUMENTATION

## Adverse Events

An adverse event (AE) is any untoward medical occurrence in a clinical investigation of a patient administered a pharmaceutical product and that does not necessarily have a causal relationship with the treatment. An AE is therefore any unfavorable and unintended sign (including an abnormal laboratory finding), symptom or disease temporally associated with the administration of an investigational product, whether or not related to that investigational product. An unexpected AE is one of a type not identified in nature, severity, or frequency in the current Investigator’s Brochure or of greater severity or frequency than expected based on the information in the Investigator’s Brochure.

The Investigator will probe, via discussion with the subject, for the occurrence of AEs during each subject visit and record the information in the site’s source documents. Adverse events will be recorded in the patient CRF. Adverse events will be described by duration (start and stop dates and times), severity, outcome, treatment and relation to study drug, or if unrelated, the cause.

**AE Severity**

The National Cancer Institute’s Common Terminology Criteria for Adverse Events (CTCAE) Version 3.0 should be used to assess and grade AE severity, including laboratory abnormalities judged to be clinically significant. The modified criteria can be found in the study manual. If the experience is not covered in the modified criteria, the guidelines shown in Table 1 below should be used to grade severity. It should be pointed out that the term “severe” is a measure of intensity and that a severe AE is not necessarily serious.

Table 1. AE Severity Grading

| **Severity (Toxicity Grade)** | **Description** |
| --- | --- |
| Mild (1) | Transient or mild discomfort; no limitation in activity; no medical intervention or therapy required. The subject may be aware of the sign or symptom but tolerates it reasonably well. |
| Moderate (2) | Mild to moderate limitation in activity, no or minimal medical intervention/therapy required. |
| Severe (3) | Marked limitation in activity, medical intervention/therapy required, hospitalizations possible. |
| Life-threatening (4) | The subject is at risk of death due to the adverse experience as it occurred. This does not refer to an experience that hypothetically might have caused death if it were more severe. |

**AE Relationship to Study Drug**

The relationship of an AE to the study drug should be assessed using the following the guidelines in Table 2.

Table 2. AE Relationship to Study Drug

| **Relationship to Drug** | **Comment** |
| --- | --- |
| Definitely | Previously known toxicity of agent; or an event that follows a reasonable temporal sequence from administration of the drug; that follows a known or expected response pattern to the suspected drug; that is confirmed by stopping or reducing the dosage of the drug; and that is not explained by any other reasonable hypothesis. |
| Probably | An event that follows a reasonable temporal sequence from administration of the drug; that follows a known or expected response pattern to the suspected drug; that is confirmed by stopping or reducing the dosage of the drug; and that is unlikely to be explained by the known characteristics of the subject’s clinical state or by other interventions. |
| Possibly | An event that follows a reasonable temporal sequence from administration of the drug; that follows a known or expected response pattern to that suspected drug; but that could readily have been produced by a number of other factors. |
| Unrelated | An event that can be determined with certainty to have no relationship to the study drug. |

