## Risk / Benefit Assessment

There are very rare, but serious risks to peripheral nerve blockade, including infection at the puncture site, bleeding at the puncture site, local anesthetic toxicity, anaphylaxis, and nerve injury. With interscalene nerve blockade, there is also a risk of Horner's syndrome, hoarseness, and respiratory distress. The more common risk of peripheral nerve blockade, occurring in less than 10% of blocks at the Orthopaedic Institute, is failure of the nerve block to provide adequate analgesia in the corresponding anatomical site. This can be easily treated postoperatively by either administration of IV pain medications or a postoperative nerve block. Patients undergoing nerve blocks are advised to protect the operative limb in a sling until numbness from the block has resolved. The numbness resulting from the nerve block is a common and desired side effect. Of note, these risks are not related to patient participation in the study, but rather are the risks of peripheral nerve blockade which patients would receive even if they were not part of the study.

Specific study risks include a potential loss of privacy for patients that are involved in the study. There is a potentially higher risk of transient paresthesia in the group receiving intraplexus interscalene nerve blocks, which we will be recording. There is also a risk with randomization that the patients will be assigned to a treatment program by chance and the treatment they receive may prove to be less effective or to have more side effects than the other study treatment or other available treatments.

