# STUDY DESIGN

## Study Overview

This is a single center, blinded, randomized trial. 208 of subjects are planned. Each subject will be administered a single injection of ropivacaine 0.5% either intraplexus or extraplexus prior to their shoulder surgery. Subjects will be assigned to the treatment group in random order. Evaluations will be taken in one-minute intervals after placement of the block until loss of motor or sensation is observed. Subjects will undergo a standardized general anesthetic. Sensory exam will be reevaluated in the recovery room. Patients will be contacted via telephone on post-operative day 1. Data from their 1 week postoperative visit will be recorded.

Screening data will be reviewed to determine subject eligibility. Subjects who meet all inclusion criteria and none of the exclusion criteria will be entered into the study.

The following treatment regimens will be used:

Experimental treatment –interscalene injection performed intraplexus (between C5-C6 nerve roots)

Comparator – interscalene injection performed extraplexus (anterior and posterior to brachial plexus in interscalene groove)

Total duration of subject participation will be two weeks. Total duration of the study is expected to be 24 months.

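### Adverse events are graded only for relationship to ropivacaine, identical in both arms, and partly by a dechallenge test that a single block dose cannot meet; the grade and its by-arm table are uninformative about technique

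*Protocol*

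**What the plan says.** On treatment, the protocol's Dosage/Dosage Regimen section specifies "25mL of ropivacaine 0.5% given for interscalene block once". Formulation of Test and Control Products gives both groups the same product and volume, and adds: "As the drug is the same for each group, it is not necessary for it to be blinded". Study Overview defines the arms by where the injection goes: between the C5 and C6 roots, or in front of and behind the plexus.

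On causality, the section AE Relationship to Study Drug states: "The relationship of an AE to the study drug should be assessed using the following the guidelines in Table 2". Table 2 has four grades: *Definitely*, *Probably*, *Possibly* and *Unrelated*. *Probably* includes the condition "that is confirmed by stopping or reducing the dosage of the drug; and that is unlikely to be explained by the known characteristics" of the patient's state. *Definitely* has the same dechallenge condition on its second route. Its first route is toxicity already known for the agent.

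The Adverse Events paragraph under Clinical Assessments puts relation to study drug on the case report form. The Adverse Events section under adverse experience reporting repeats this and asks for the cause when an event is unrelated. Analysis of Secondary Endpoints then plans a table by treatment group showing patient counts, rates, and "the severity and relationship to study drug".

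Risk / Benefit Assessment names one harm that may differ between arms: "There is a potentially higher risk of transient paresthesia in the group receiving intraplexus interscalene nerve blocks".

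**The concern.** A causality grade is useful in a comparative trial when it refers to something that differs between the arms. Here the drug is common to both and the needle position is what differs. The scale asks about the former and has no place for the latter. Two of its four grades also rest on a dechallenge test designed for repeated dosing.

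At stake is the case-level safety record and one planned table. A paresthesia or deficit caused by the needle may be entered as only possibly related, or unrelated, to study drug. Someone reading the relationship column alone could take that as reassurance about the intraplexus approach. The grade is assigned when the event is recorded, so a later analysis plan could change the table but could not easily recover a procedure rating that was never collected.

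**Working it through.** The point depends on no figure in the protocol, so the check sets the sections side by side.

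1. **What is randomised.** Study Overview: injection location. Formulation of Test and Control Products: same drug, same volume. A rating of relationship to the drug therefore does not address the randomised factor.

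2. **Whether dechallenge is possible.** Dosage/Dosage Regimen gives the dose once. For an event appearing after the injection is complete, no remaining dose can be stopped or reduced.

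3. **What each grade needs, for an event arising after the block:**

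| Grade in Table 2 | Dechallenge needed? | Reachable? |
| --- | --- | --- |
| *Definitely*, route 1 (known toxicity of the agent) | No | Yes |
| *Definitely*, route 2 | Yes | No |
| *Probably* | Yes | No |
| *Possibly* | No, but the event must fit a response pattern of the drug | Yes, for drug-like events |
| *Unrelated* | No, but a link to the drug must be excluded with certainty | Yes, if certain |

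One grade of four is closed and one is left with a single route.

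4. **Where a needle-related event goes.** A mechanical paresthesia need not follow a pattern known for ropivacaine, so *Possibly* fits badly. Drug and needle arrive in the same procedure, so certainty that the drug played no part will often be lacking, and *Unrelated* fits badly too. The rater has to choose between two definitions that may both fail. Neither choice records that the procedure was the suspected cause.

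5. **Whether another field fills the gap.** The reporting section asks for a cause only when the event is unrelated. An event graded *Possibly* triggers no such entry, and Analysis of Secondary Endpoints does not plan to tabulate the recorded cause.

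6. **What is not affected.** Safety Evaluations lists paresthesias, nerve injury, Horner's syndrome, hoarseness and other block harms as incidences with no causality grade. The synopsis and Secondary Objectives also list incidence of paresthesias. Analysis of Secondary Endpoints tabulates all adverse events by group and gives tests for categorical data. Serious Adverse Experience Reporting and the Institutional Review Boards section make reporting of serious events independent of causality.

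**The case against.** The strongest reply is that randomisation already does the attribution. Treatment group means technique, all events are counted by group, and nothing restricts the comparison to related events. An excess of paresthesia in one arm would be visible whatever box was ticked. This stands. A reader might infer from Table 2 that technique-related harm cannot be attributed at all in this trial; the incidence comparisons show that this is not so.

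A reader might also infer that every needle-related event must end in *Possibly* or *Unrelated*, or that the protocol expects nerve injury to differ between arms. Neither is supported. The first route to *Definitely* stays open, and *Unrelated* demands certainty. Risk / Benefit Assessment raises a possible difference only for transient paresthesia; it lists nerve injury among the very rare risks of any such block.

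It can further be said that *Probably* is not strictly impossible. Patients are kept awake to report symptoms on injection, and a symptom might ease if the injection were paused. The protocol describes no such step, and this would not help with events noticed after the dose is complete, so it narrows the point without removing it.

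Finally, the relationship column is descriptive, no test is planned on it, and the cause of unrelated events is recorded. That keeps the consequence small. It does not make the grade informative. For rare harms, group counts say little: with no events in 104 patients, the one-sided 95% upper limit is 1 − 0.05^(1/104) = 0.028, or about 2.8%, assuming all 104 in an arm are assessed. There, case-level assessment carries more of the weight.

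**Conclusion.** The point holds as a minor one. The per-event causality grade and its planned tabulation by arm refer to a drug that does not differ between arms, and two of the four grades contain a condition that cannot be met once the block dose has been given. Both are therefore uninformative about technique, and needle-related events can be filed under grades that obscure their likely source.

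The consequence is confined to that grade and that column. The primary endpoint, the sample size, the incidence of adverse events and paresthesias by arm, and the reporting of serious events are unchanged. The conclusion assumes that Table 2 is applied as written and that the event arises after the injection is complete. No blinding change is needed for it: the Blinding section already keeps investigators unaware of assignment, and Other Clinical Procedures assigns block assessment to an investigator not involved in placing it.

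**What to change.** - In both Adverse Events sections, in AE Relationship to Study Drug and on the case report form, add a rating of relationship to the block procedure, meaning needle placement and injection, beside the rating for study drug.
- In Table 2, delete the stop-or-reduce condition from *Definitely* and *Probably*.
- In Analysis of Secondary Endpoints, add a tabulation of procedure-related events by treatment group.

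The cost is one form field and revised table wording. No visit, endpoint or sample size changes. The field should be in place before events are recorded, because the rating is made at that time.
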